### Statistical considerations

#### Sample size

For the primary endpoint in this pilot study, time to treatment decision for lung cancers, if we expect an 11-day advance in time to first treatment decision, with a standard deviation of 14 (previous audit data suggest this degree of variation), 26 cancers in each group will confer 80% power (two-sided testing, 5% significance level), for the internal randomised comparison. We expect around 50 cancers per year in Homerton University Hospital (HUH), so we will have adequate power for this difference. A reduction in time to diagnosis of 2 weeks was found to improve mortality of lung cancer patients so this difference could be clinically significant in the current pilot study [34]. If we anticipate a 12-day, instead of an 11-day advance in diagnosis, we would only need 22 in each arm, 44 cancers in all, for 80% power. For the external comparison, assuming that Newham University Hospital has a similar number of lung cancers per year, therefore, we would have close to 90% power for the same difference and standard deviation. If we also compare times to diagnosis for all persons referred to the pathway (lung cancer and non-lung cancer diagnoses), previous data suggest an average of 18 days and a standard deviation of 14. If the intervention improves this by 7 days on average, with a standard deviation of 15, we would need 73 subjects in each group referred to the pathway to achieve 80% power (two-sided testing, 5% significance level). Thus, both the internal and external comparisons will be adequately powered.

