### Randomisation

Intervention is at an institutional level; individual patients will not be randomised. Half-day sessions will be randomised to intervention or standard practice, using a randomisation list provided by the study statistician. This is in line with previous studies that have examined the timing or order of X-ray reading but where all examinations are requested as part of routine clinical care and receive reports from the same practitioners [30].

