### Outcome measures

The primary outcome is to test the impact of radiographer immediate reporting of GP CXRs, with immediate CT where appropriate, on time from performance of the CXR to treatment (with intermediate time points)/discharge for lung cancer.

Secondary outcome measures include:Measurement of the effect on the speed of the lung cancer pathway:
(i)6-and 12-month survival (lung cancer and all-cause)(ii)Number of emergency admissions for lung cancer(iii)Performance status at time of decision to treat(iv)Stage at diagnosis of lung cancer
Measurement of the effect of the pathway on efficiency including:
(i)The impact of immediate GP CXR reporting on the number of urgent respiratory cancer (2WW) referrals(ii)The accuracy and usefulness of radiographer CXR reporting in clinical practice(iii)The cost-effectiveness of radiographer reporting(iv)The influence of immediate GP CXR reporting, with immediate CT where appropriate, on the number of first 2WW appointments with all radiology results available
Measurement of the number of repeat CXRs performed in a timely fashion for suspected infectionThe effect of immediate reporting of GP CXRs on patient satisfaction

In addition to comparison as per randomisation within Homerton University Hospital, primary outcomes will be compared with a neighbouring hospital, Newham University Hospital.

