## Discussion

The current study will determine the effect of immediate reporting of CXRs referred from GP, with immediate CT where appropriate, on the time to diagnosis of lung cancer. Although only one part of the patient pathway, immediate GP CXR reporting could positively impact lung cancer diagnosis and outcomes in at least three ways: firstly, by providing an immediate CXR report and initiating earlier further investigation including CT, the time to diagnosis will be shortened. There is debate within the academic literature as to the significance of this in terms of improvements in early survival times, performance status and reducing emergency admissions [34]. The current study will examine this, both with internal and external comparison. Secondly, the efficiency of the service may be improved by reducing the number of lung cancer pathway referrals through early provision of an alternative diagnosis, which in turn means less time for patient anxiety and distress. Thirdly, the proposal may release consultant radiologist time that can instead be used to interpret more complex cross-sectional imaging and support interventional procedures including lung biopsy. A reduction in average time to diagnosis for lung cancer will help centres meet the ambitious target of 90% of lung cancer patients definitively diagnosed within 28 days by 2020 [14].

Diagnostic capacity is a significant barrier to improved outcomes for cancer patients [14, 36], with prompt radiology reports a particular issue across England [15, 18].

The limitations of the current study include the fact that the intervention occurs only at a single clinical site at which the diagnostic aspect of the lung cancer pathway is already relatively streamlined. This is addressed by external comparison with a neighbouring hospital with similar patient characteristics and a comparable number of lung cancers diagnosed annually.

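### The comparison among all persons referred to the pathway uses a group formed after randomisation by a referral that immediate reporting is expected to reduce, so it probably understates the benefit by an unknown amount

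*Protocol article*

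**What the plan says.** The Randomisation section fixes the unit: "Half-day sessions will be randomised to intervention or standard practice". The Sample size section first sizes the cancer-only endpoint (26 cancers per group), then adds a comparison of time to diagnosis: "If we also compare times to diagnosis for all persons referred to the pathway (lung cancer and non-lung cancer diagnoses"). Its inputs are "previous data suggest an average of 18 days and a standard deviation of 14" and "If the intervention improves this by 7 days on average, with a standard deviation of 15", and the result is that "we would need 73 subjects in each group referred to the pathway to achieve 80% power". The section ends by stating that the internal and external comparisons will both be adequately powered. The Data analysis section assigns simple t tests to times to diagnosis.

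Elsewhere the protocol expects the intervention to change who is referred. The Abstract gives fewer inappropriate urgent referrals as a reason for immediate reporting. The Outcome measures section lists as a secondary outcome "The impact of immediate GP CXR reporting on the number of urgent respiratory cancer (2WW) referrals". The Discussion expects a gain in efficiency from "reducing the number of lung cancer pathway referrals through early provision of an alternative diagnosis".

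**The concern.** Referral to the pathway happens after the session is randomised and after the film is reported, and the number of referrals is itself a trial outcome. Restricting a comparison of times to referred patients conditions on something the intervention is meant to alter.

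The Discussion's mechanism suggests a direction. Referrals avoided through an early alternative diagnosis would mostly be patients without cancer whose question was settled quickly. In an immediate session such a patient may never enter the referred group, while a similar patient in a control session may be referred and counted. The immediate arm would then lose some of its shortest times and keep a higher proportion of cancers. A t test does not correct for this.

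At stake is the only calculation in the Sample size section that covers non-cancer patients. The Abstract's hypothesis and the primary outcome both include discharge from the pathway, so this comparison carries weight although it is introduced as an addition.

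**Working it through.** **Inputs from the Sample size section.** Control mean 18 days; gain 7 days, so a true immediate-arm mean of 18 − 7 = 11 days; planning SD 15; two-sided 5%; 80% power; 73 per group.

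**The plan's own figure.** Normal approximation: n = 2 × (1.960 + 0.842)² × 15² / 7² = 72.1 per group. Based on the t distribution, n = 73.05, and 73 per group gives 80.0% power. The stated 73 is reproduced; the arithmetic is sound and the problem lies in the set of patients.

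**Assumptions not in the protocol.** Let f be the share of would-be-referred immediate-arm patients whose referral is avoided, in excess of any such share in control. Let m be the mean time of those patients.

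- Mean of those still referred: (11 − f·m) / (1 − f)
- Apparent gain: 18 − (11 − f·m) / (1 − f)
- Group sizes: 73 control and 73(1 − f) immediate
- Power: two-sided t test, SD 15 in both groups

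Worked example, f = 0.20 and m = 1: (11 − 0.2) / 0.8 = 13.5; apparent gain 18 − 13.5 = 4.5 days; 58.4 immediate-arm patients; power 40%.

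| f | m (days) | Mean of those still referred | Apparent gain (days) | Power |
|---|---|---|---|---|
| 0 | – | 11.0 | 7.0 | 80% |
| 10% | 3 | 11.9 | 6.1 | 66% |
| 10% | 0 | 12.2 | 5.8 | 61% |
| 20% | 1 | 13.5 | 4.5 | 40% |
| 30% | 3 | 14.4 | 3.6 | 25% |
| 30% | 0 | 15.7 | 2.3 | 13% |
| 10% | 11 | 11.0 | 7.0 | 78% |
| 20% | 15 | 10.0 | 8.0 | 85% |

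The last two rows show the limits of the argument. If the leavers average 11 days, the mean is unbiased and power falls only through the smaller group. If they are slower than 11 days, the gain is exaggerated.

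**When would the sign reverse?** Setting the apparent gain to zero gives f = 7 / (18 − m): 39% for m = 0, 41% for m = 1, 47% for m = 3 and 54% for m = 5.

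**Check with the fastest non-cancer patients removed.** Assume cancers are 25% to 33% of referrals, cancers take 15 days longer than non-cancers, non-cancer times follow a gamma distribution of shape 1 or 2, and the immediate arm already has its 7-day gain (mean 11). Removing the fastest 20% of non-cancer patients leaves an apparent gain of 5.2 to 5.5 days. Removing the fastest 50% leaves 1.7 to 2.9 days.

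**The case against.** Five points can be made against this.

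1. **Referral is not defined.** The Background treats the reporting of a mass on the film as often the first step in the pathway, and the Outcome measures section starts the clock at the X-ray. If being referred means having a suspicious film, a same-day exclusion already counts as a short time and the selection is much weaker. This stands as a limit on size. The Discussion, however, speaks of reducing pathway referrals by an early alternative diagnosis, which fits a step after the film better.

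2. **Controls can also be cleared before referral.** The Control section says Homerton controls with a suspicious film are offered CT through radiology, and some receive an immediate report. This stands: only the excess over control matters, which is how f is defined above.

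3. **Nothing says that patients cleared by a same-visit CT are never referred.** One secondary outcome counts first urgent appointments with all radiology results available, so some patients attend after imaging. This stands; the most that can be said is that they may not be referred.

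4. **The comparison is an addition in a self-described pilot.** The cancer-only endpoint in the Sample size section is indeed untouched by this mechanism. But the added comparison is sized, and it contributes to the claim of adequate power.

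5. **Analysis sets are often left to a statistical analysis plan.** True in general, but here the protocol itself names the set and sizes it.

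A reader might infer that the benefit will be hidden or reversed. The documents do not support that. They give no avoided share, reversal needs about 39% or more excess avoided referrals even at 0 days, and removing the fastest non-cancer patients from an arm that has the gain shrinks it without cancelling it.

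**Conclusion.** The point holds as a loss of randomised protection, with a probable bias against the intervention of unknown size. It rests on the protocol's own statements that sessions are randomised first, that the added comparison is restricted to referred patients, and that referrals are expected to fall.

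The range of 6.1 down to 2.3 days, with power of 66% down to 13%, is an illustration. It assumes a 10% to 30% excess of avoided referrals at 0 to 3 days, a true 7-day gain and SD 15. The direction depends on the leavers being quicker than 11 days, which the Discussion's mechanism makes likely but does not establish.

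The adequate-power statement is not supported for this comparison. It assumes equal groups of 73 referred patients although the intervention is meant to make one group smaller, and the Sample size section gives no expected number of referrals to set against the 73. The external comparison is also exposed: Newham has no straight-to-CT service, so its referred group is formed differently.

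**What to change.** **Internal comparison.** Define the set by a criterion that does not depend on the arm: every eligible GP chest X-ray read as suspicious for cancer on the consultant report, which is made for all films and blinded to the radiographer's report. Analyse by allocated session, whether or not a referral followed. Run the clock from the X-ray to the date cancer is diagnosed or excluded, so that an avoided referral counts as a short time. The radiographer's read should not define the set, because it is made under the allocated condition.

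**External comparison.** Newham has no reporting radiographers, so use the consultant-reported suspicious film as the matching criterion there, and label the comparison non-randomised.

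**Sample size.** For a 7-day gain and SD 15 the figure of 73 per group stands if those values also apply to the new set. Set it against the expected yearly number of such films, or withdraw the adequate-power statement for this comparison.

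**Cost.** A change of protocol and analysis wording. At Homerton the blinded consultant read is already planned for every film. The small downside is that outcome dates must be looked up for patients who were never referred.

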**Fig. 2 Fig2:**
[figure not shown]
Schedule of enrolment, interventions and assessments. C*XR* chest X-ray, *CT* computed tomography scan, *when required

The diagnostic aspect of the lung cancer pathway at Homerton University Hospital is relatively streamlined. To enable comparison with radiology service delivery at other institutions’ time to diagnosis (immediate and standard CXR reporting) will be compared with Newham University Hospital (Fig. 2). This adjacent hospital has comparable patient demographics, a similar number of lung cancer patients per year and is of comparable size. Newham does not currently have CXR-reporting radiographers and does not offer a straight-to-CT service for CXRs suspicious for lung cancer.

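### The near-90% power of the external comparison is power for a difference between two hospitals from any cause, not for the effect of immediate reporting

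*Protocol article*

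**What the plan says.** All places are in the Protocol article.

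- **Randomisation.** Half-day sessions at Homerton are randomised to immediate or standard reporting. Nothing is randomised between hospitals.
- **Trial design.** Homerton's diagnostic pathway is described as relatively streamlined. Newham is described as comparable in demographics, size and lung cancer numbers, but "Newham does not currently have CXR-reporting radiographers and does not offer a straight-to-CT service for CXRs suspicious for lung cancer". Both the immediate and the standard Homerton groups are to be compared with it.
- **Outcome measures.** Besides the randomised comparison, "primary outcomes will be compared with a neighbouring hospital, Newham University Hospital".
- **Sample size.** The internal calculation reads "if we expect an 11-day advance in time to first treatment decision, with a standard deviation of 14", with 26 cancers per group for 80% power. The external figure, "assuming that Newham University Hospital has a similar number of lung cancers per year", is close to 90% for the same difference and SD. The section closes with "Thus, both the internal and external comparisons will be adequately powered".
- **Data analysis.** Times are compared by simple t tests.
- **Discussion.** The stated limitation is that the intervention runs at one site whose pathway is already efficient. The text continues: "This is addressed by external comparison with a neighbouring hospital with similar patient characteristics".

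**The concern.** The internal and external comparisons estimate different things, yet the protocol gives them the same 11-day effect and the same verdict on power. In the internal comparison, randomised sessions at one hospital differ in the timing of the report and what follows from it. In the external comparison, the immediate-report patients differ from the Newham patients in that respect and also in hospital, in who reports the film, and in whether a suspicious film leads straight to CT. With one hospital on each side, no analysis of these data can separate those components.

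At stake is what a positive external result would be taken to show. The external test has the larger sample, and on the protocol's own description it probably has the larger contrast, so it is the likelier of the two to reach significance. The Background says that the study could serve as a pilot for a larger multisite evaluation if results are positive. If the external result counts towards that decision as evidence for immediate reporting, the decision could rest on a difference that existed before the study began.

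**Working it through.** **Inputs from the Sample size section.** Difference 11 days; SD 14; two-sided 5% level; about 50 cancers a year at Homerton, so about 25 per internal arm; a similar number, about 50, at Newham.

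**1. Reproduce the internal sample size.** n per group = 2(1.960 + 0.842)² × 14² / 11² = 2 × 7.85 × 196 / 121 = 25.4, so 26. This matches the protocol.

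**2. Reproduce the external power.** For 25 against 50:

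- SE = 14 × √(1/25 + 1/50) = 14 × 0.2449 = 3.43 days.
- λ = 11 / 3.43 = 3.21.
- Normal power = Φ(3.21 − 1.96) = Φ(1.25) = 89.4%.
- Noncentral t with 73 degrees of freedom: 88.6%.

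Using 26 against 50 gives 90.1% (t: 89.4%). Using all 50 Homerton cancers against 50 gives 97.6% (t: 97.3%), which does not match the stated figure. The protocol's figure is therefore evidently the immediate arm against Newham, and it is correct as arithmetic.

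**3. What the 11 days stands for.** Write the external difference as

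(immediate − Newham) = (immediate − standard) + (standard − Newham).

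The first term is the effect of immediate reporting. The second is the effect of site and of Homerton's other services. Using the intervention's 11 days for the whole left-hand side, and reading the result as power for the intervention, requires the second term to be zero. The protocol gives reasons to expect otherwise. Under Control, Homerton's standard sessions already have a maximum turnaround of one working day and a CT offered through the radiology department, while Newham has neither reporting radiographers nor straight-to-CT.

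**4. What the test does when the first term is zero.** The SD of 14 enters as a patient-level SD only; there is no between-hospital component, and one hospital per side could not supply one. The t test then responds to the second term alone. With critical value 1.993, an observed gap of 1.993 × 3.43 = 6.8 days is significant. The offsets below are **assumptions**; the documents give none.

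| Assumed site offset (days) | λ = offset / 3.43 | Probability that the t test is significant, 25 v 50, no effect of immediate reporting |
|---|---|---|
| 0 | 0 | 5% |
| 3 | 0.87 | 14% |
| 5 | 1.46 | 30% |
| 7 | 2.04 | 52% |
| 11 | 3.21 | 89% |

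The last row makes the point without choosing a plausible offset: an 11-day gap due wholly to hospital would be declared significant exactly as often as one due wholly to immediate reporting.

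**5. Internal comparison, for scale.** With 25 per arm rather than 26, power is 79.3% (normal) or 77.7% (t), marginally below the 80% target.

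**The case against.** The strongest reply is that nothing is miscalculated and little is hidden. Trial design gives the external comparison a legitimate purpose, to set Homerton's service beside delivery elsewhere, and names the two service differences openly. It already plans to compare both Homerton groups with Newham. Only the internal comparison is called randomised, and the primary endpoint is sized on it. Faster CT is also part of the defined intervention, so a contrast that includes it is not wholly foreign to the question.

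Most of that stands, and it rules out several stronger readings that a reader might infer:

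- *The hospitals differ in reporting speed and throughout their pathways.* The text shown gives no turnaround time for Newham. It names two service differences and a more streamlined Homerton pathway, and no more.
- *The Discussion claims that the external comparison identifies the causal effect.* It does not say so. The limitation it raises is largely about generalising from an efficient site, and a less streamlined comparator has some bearing on that.
- *The percentages in step 4 are the trial's error rates.* They are ordinary power for a real hospital difference of assumed size.
- *The internal comparison is badly under-powered.* The shortfall is about one cancer per arm.
- *External eligibility is defective, or a pre-study period is required.* Eligibility at the comparator is a detail that an article may leave to the full protocol, and a before-and-after extract would be a new design element.

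The reply does not reach the Sample size section, where the intervention's effect is transferred to the external contrast and both are called adequately powered without saying for what. Nor does the CT argument separate the components, because Homerton's control sessions also lead to a CT arranged by radiology. An analysis plan not shown may adjust for patient characteristics, but that cannot separate hospital from service with one hospital per side.

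**Conclusion.** The point holds as a matter of interpretation. The close-to-90% figure is correct for 25 against 50 independent patients, and it is the power to detect an 11-day difference between Homerton's immediate arm and Newham from any cause. It cannot be offered as power for the effect of immediate reporting. This conclusion rests only on the design as described: randomisation within Homerton, one comparator hospital, and named service differences.

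The 14%, 30% and 52% rest on assumed offsets of 3, 5 and 7 days, and they show how readily the test responds to a site difference. Likewise, saying that the single-site limitation is addressed goes too far: the intervention still runs at one hospital, and the comparison gives context. The external comparison is worth keeping under an accurate label, and the change should be made before the results are interpreted.

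**What to change.** 1. **Sample size.** Limit the statement of adequate power for the effect of immediate reporting to the randomised internal comparison. State that the external figure is power to detect a whole-service difference between two hospitals, whatever its cause.
2. **Outcome measures and Data analysis.** Name the internal comparison as the only primary comparison. Report Newham, Homerton standard and Homerton immediate side by side. Credit only immediate minus standard to immediate reporting, and label standard minus Newham as the combined effect of site and its other services, including radiographer reporting and straight-to-CT.
3. **Discussion.** Replace the claim that the limitation is addressed with a statement that the external comparison gives descriptive context only.

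The cost is wording and table labels. No new data are needed, because Trial design already plans to compare both Homerton groups with Newham. The downside is a less striking external claim.
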